## Recruitment

Potential study volunteers will be primarily recruited through the UCSF campus community (students, staff, and faculty), as well as members of the general public. Members of the UCSF community can be easily reached for directly observed dosing of study drug. Study visits will occur on the UCSF Parnassus campus, at the San Francisco Health Department, or another location according to feasibility and convenience for the participants. Recruitment materials will be approved by the UCSF Institutional Review Board. Information about this study will be posted to a variety of UCSF electronic email listservs to assist with study recruitment. Additional recruitment methods may include advertising through local newspapers, using direct outreach, and through the Internet.

Interested subjects will be pre-screened over the phone or in person. If preliminarily eligible, they will be scheduled for an in-person screening visit in a private location at UCSF or at the SFDPH research clinic.

# STUDY PRODUCT

## Formulation

Tenofovir disoproxil fumarate (Viread®, TDF) oral tablet, is a fumaric acid salt of bisisopropoxycarbonyloxymethyl ester derivative of tenofovir. Each tablet contains 300 mg of TDF, which is equivalent to 245 mg of tenofovir disoproxil. Tenofovir disoproxil fumarate should be stored at 25ºC (77ºF). Excursions are permitted between 15ºC and 30ºC (59ºF and 86ºF)

## Dispensing and Dosing

Study participants will receive study drug using modified directly observed therapy (mDOT) conducted by a research associate (RA) trained in mDOT procedures. Study product will be dispensed to enrolled participants, upon receipt of a written prescription from an authorized prescriber. Participants will be randomized to one of six study regimen sequences (see section 7.5). Each participant’s study sequence will consist of three dosing periods of 6 weeks each, with a break of at least 3 weeks between dosing periods. For UCSF students, each study period will occur during an academic quarter, with a break between dosing periods of several weeks corresponding to the vacation breaks between quarters. The total study duration will be approximately five or more months for non-students, and approximately 36 weeks for UCSF students. Participants will take pills according to the dosing schedule designated by their randomized sequence (see section 7.5 for details) and meet with study staff for mDOT as described below (see section 7.8). Dosing times will be recorded by the study staff for the directly observed and telephone mDOT doses in a dosing log. Participants will be provided a one-week pre-packed emergency supply of medication to be used if they cannot or fail to make a scheduled visit with the study staff. Study drug may be taken without regard to meals.

## Supply

Tenofovir disoproxil fumarate 300 mg tablets will be supplied by Gilead Sciences, Inc. (Foster City, CA, USA). Tablets will be packaged in bottles of 30 tablets with a child-resistant screw cap. In addition to the tablets, each bottle contains a silica gel dessicant to protect the product from humidity and polyester packing material that cushions it during handling and shipping. Gilead will prepare bottles of study agent that are each labeled with expiry date and bottle ID number, which will be assigned to participants at the time of randomization during the enrollment visit.

## Accountability

Study drug will be stored at the San Francisco Department of Public Health HIV Research Section study site in a secured location in double-locked cabinets. The investigator and designated staff will maintain complete records of all study products received from Gilead and subsequently dispensed. At the end of the study, a final drug accounting of unused study material will be performed on proper log documents. All unused study product will either be returned to Gilead or destroyed according to site-approved procedures.

# STUDY PROCEDURES

## Study Flow Chart

| **Procedure** | **SCR** | **ENR** | **D1** | **MIDPT** | **ENDPT** |
| --- | --- | --- | --- | --- | --- |
|  |  |  |  |  |  |
| Informed Consent | X |  |  |  |  |
| Baseline Medical History | X |  |  |  |  |
| Full Physical Exam |  | X |  |  |  |
| Sx-directed Physical Exam | X |  | X | X | X |
| Adverse Event Assessment |  |  |  | X | X |
| Adherence counseling |  |  | X | X |  |
| CBC, chemistries | X | X | X | X | X |
| Urine dipstick | X | X | X | X | X |
| Urine pregnancy test (women only) | X | X | X | X | X |
| HBSAg, anti-HBs, anti-HBc† | X |  |  |  | X |
| HIV-1 rapid test | X | X | X | X | X |
| Hair collection |  | X |  |  | X |
| PBMC/plasma storage |  | X |  |  | X |
| Serum storage |  | X | X | X | X |
| Stipend | X | X | X | X | X |

**SCR = screening; ENR = enrollment; D1 = first dose day, MIDPT = midpoint visit with target date 21 days after first dose day , ENDPT = endpoint visit with target date 42 days after first dose day window period for each scheduled visit is ± 5 days of the target visit date**

*** Intensive PK sampling will be performed after 28 days of study drug on the 7 days/week arm. The window period for the intensive PK visit is ± 5 days.**

**†Hepatitis serological testing will be done at the screening visit and at the final endpoint visit for individuals who are susceptible to hepatitis B at baseline.**

**†HBV DNA testing will be performed for individuals who have isolated hepatitis B core antibody positivity (HBSAg negative, anti-HBs negative, anti-HBc positive)**

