## Drug-Administration Flowchart

| **Procedure** | **Weekly follow-up (6 wks)** | | | | | | |
| --- | --- | --- | --- | --- | --- | --- | --- |
|  | **M** | **T** | **W** | **Th** | **F** | **S** | **Su** |
| **DOT (7 doses/week)** | **X** | **X** | **X** | **X** | **X** |  |  |
| **Phone mDOT (7 doses/week)** |  |  |  |  |  | **X** | **X** |
| **DOT (4 doses/week)** | **X** | **X** |  | **X** | **X** |  |  |
| **DOT (2 doses/week)** |  | **X** | **X** |  |  |  |  |

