## Enrollment

At the enrollment visit, the participant’s laboratory results will be reviewed with the study participant. Another rapid HIV test will be performed. All eligibility criteria will be reviewed and confirmed. If the participant is eligible, he or she will be enrolled and randomly assigned into one of 6 arms of this 3 condition cross-over study (see section 7.5). Each arm will be stratified by gender. The 4 doses/week group will occur on Monday, Tuesday, Thursday, and Friday, and the 2 doses/week will occur on Tuesdays and Wednesdays. Enrollments may be scheduled on any day of the week, but study drug initiation will occur at the beginning of the week (Monday for the 4 and 7 doses/week groups and Tuesday for the 2 doses/week group).

Blood, hair, and urine specimens will be collected at the enrollment visit. Participants will receive a detailed daily dosing schedule and visit calendar for all 3 periods of their study participation. The participants’ cell phone number, other phone numbers and a list of places where they might be located will be obtained along with a follow-up plan in the event that the participant is not at the designated meeting place.  A one-week supply of back-up medication will be provided in the event that participants are unable to be seen for directly observed doses. Study participants will be provided access to a 24 hour, 7 days/week emergency pager to discuss any potential study related adverse events with a study clinician.

| **Enrollment Visit** | |
| --- | --- |
| Component | Procedure/Analysis |
| Administrative | - Assign Participant ID or Screen failure ID - Review/update locator information - Provide lab results to participant - Confirm eligibility - Follow procedures for randomization assignment - Explain mDOT procedures - Confirm cell-phone number for doses observed by phone and reminder text messages - Provide dosing schedule and visit calendar to participant - Schedule next study visit with RA - Provide reimbursement for visit |
| Clinical | - Update medical history - Update list of concomitant medications - Perform full physical exam - Provide counseling   - HIV pre- and post-test counseling |
| Urine | - Collect urine sample   - Qualitative hCG   - Dipstick UA (and full UA with microscopy if greater than trace protein, glucose, heme, or leukocytes) |

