## Directly Observed Visits and Phone Visits

Participants will receive modified directly observed dosing of oral TFV from a study staff according to the dosing schedules shown in section 7.2. Doses for all participants will be scheduled to occur at roughly the same time each day (e.g. 3pm). Ingestion of all Monday through Friday scheduled doses will be directly observed by study staff at an agreed-upon location on the UCSF campus, at the SFDPH research clinic, or at another predetermined location to maximize convenience for the participant. For weekends, holidays, and other foreseen-in-advance dates for self-dosing, study staff will provide pills to participants at the immediately preceding dose visit. Ingestion of unobserved doses will be confirmed via phone or text message mDOT. Participants will be asked to text or phone same-day confirmation of when they self-dose; if confirmation has not been received by a predetermined time, study staff will text and/or call asking for confirmation to help ensure that the doses are taken. Study staff will also send participants reminders as needed by email, text message, or telephone, for directly observed dose visits or to take back-up (emergency pack) medication if they miss a dosing visit. Dosing times will be recorded by the study staff for directly observed doses and telephone mDOT.  Study staff will confirm the dates and times of all self-administered doses at their next meeting with the subject.  Stipends will be provided at the completion of each dosing visit or clinical visit.

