## Intensive PK Specimens

After 4 weeks of dosing on the 100% adherence condition, all participants will undergo a 24 hour intensive-PK study protocol (requiring an approximately 25-hour-long hospital stay) to evaluate steady-state effects of TFV in plasma. This visit will take place at the Clinical Resource Center (CRC) associated with UCSF/Moffitt Hospital.

The participant’s usual diet will be ascertained by phone prior to the PK visit, and simulation of the usual diet will be undertaken in the CRC during PK sampling. During the week before the PK study visit, the participant will complete questionnaires ascertaining current medication and substance use patterns, current dietary patterns, and current menstrual, contraceptive, and obstetric history, if applicable. An initial blood level will be drawn (“0” timepoint) and consumption of one dose of oral tenofovir will be witnessed. A series of blood samples will then be collected into EDTA tubes at 0, 0.25, 0.5, 1, 1.5, 2, 3, 4, 6, 8, 10, 12, 16, and 24 hours post-dose after witnessed dosing.

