## Study Primary Endpoint and Predictor Variables

Consistent with the primary study objectives, the following primary endpoint will be assessed:

- Tenofovir hair concentration: Tenofovir hair levels will be determined from a specimen containing 150-200 hairs collected at enrollment and on the last day of each period. For each participant, absolute hair levels and ratios of hair levels between conditions (7 vs. 4 doses/week, 4 vs. 2 doses/week, and 7 vs.2 dose/week) will be determined.

The following will be primary predictor variables:

- Dosing condition: The dosing condition will be examined as an ordinal variable: 2, 4, and 7 doses/week. We will also use actual percentage of total doses (by directly observed recorded doses and self-administered recorded doses) taken over the 6 week period as a continuous predictor of hair levels.
- PK parameters: The primary predictor variable of total exposure (PK contribution) will be oral clearance (CL/F). This variable is estimated by the equation “dose/AUC,” where AUC is the area under the plasma-concentration time curve for each intensive PK sampling procedure. Other parameters of drug exposure that will be evaluated as predictor variables include the concentration at the end of the dosing interval (trough or C_min_), peak plasma level (C_max_), and AUC alone. These PK variables will be calculated using non-compartmental methods.

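### The intensive PK visit's target day is a Monday, right after the week's two self-reported doses, and nothing steers it to a better day in its window

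*Protocol*

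**What the plan says.** - **Start day.** Section 7.4: "study drug initiation will occur at the beginning of the week (Monday for the 4 and 7 doses/week groups".
- **PK timing.** Section 7.1: "Intensive PK sampling will be performed after 28 days of study drug on the 7 days/week arm", and "The window period for the intensive PK visit is ± 5 days". Section 8.7 repeats the timing: "After 4 weeks of dosing on the 100% adherence condition, all participants will undergo a 24 hour intensive-PK study protocol". Section 7.7 also says after 4 weeks of dosing. None of the three sections names a weekday.
- **Observation.** Section 7.8: "Ingestion of all Monday through Friday scheduled doses will be directly observed by study staff". The flowchart in section 7.2 puts Saturday and Sunday in the row "Phone mDOT (7 doses/week". Section 7.8 adds: "Ingestion of unobserved doses will be confirmed via phone or text message mDOT".
- **Use of the profile.** Section 10.1: "The primary predictor variable of total exposure (PK contribution) will be oral clearance (CL/F", computed as dose divided by AUC from the PK session. Cmin, Cmax and AUC are further predictors. Section 8.7 describes the profile as a steady-state one.

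**The concern.** Dose divided by the 24-hour AUC equals CL/F only at steady state, and that depends most on the last one or two doses before the profile. At the target day these are the doses known only from the participant's own report. The background (section 3.1) is itself wary of self-reported adherence, and that is why observed dosing was chosen.

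A participant who missed Sunday's dose and reported it as taken would look like a fast clearer with a low AUC and a low trough. Each participant has one profile, which serves all three dosing conditions, and there are 24 participants, so the error is not averaged out. The actual-percentage dose variable in section 10.1 does not correct it, because self-administered recorded doses count as taken.

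The error need not be pure noise. The 4 and 2 doses/week schedules contain no weekend doses. Someone who habitually skips weekends would therefore have a falsely high CL/F and lower hair levels in the 7 doses/week condition only. That would resemble the effect modification by clearance that the second primary objective looks for.

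**Working it through.** The protocol gives no figure for this point to reproduce.

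**Calendar.** Count days from the first dose (day 0, a Monday). 28 = 4 × 7, so day 28 is a Monday. The window is day 23 (Wednesday) to day 33 (Saturday). Thursdays and Fridays fall on days 24, 25, 31 and 32, and each follows at least three weekday doses. If the 28th dosing day is meant, the target is Sunday (day 27), after Saturday's self-reported dose, and the window (days 22 to 32) still contains all four days.

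**Inputs.** Plasma half-life 17 h (sections 3.1 and 3.2.5). Cmax 296 ng/mL and AUC 2287 ± 685 ng·hr/mL (section 3.2.5). Assumption: a share f of the AUC lies in the terminal phase, with f from 0.5 to 1.0.

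**Formula.** By linear superposition, with a = exp(−ln2 × 24/17) = 0.376, a dose missed n days before the profile removes f × aⁿ × (1 − a) of the steady-state 24 h AUC. CL/F is then multiplied by 1/(1 − loss).

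- Sunday missed, Monday profile: 0.376 × 0.624 = 0.235 at f = 1, and 0.117 at f = 0.5.
- Saturday missed, Monday profile: 0.141 × 0.624 = 0.088 at f = 1, and 0.044 at f = 0.5.
- Both missed, Thursday profile (n = 4 and 5): (0.0200 + 0.0075) × 0.624 = 0.017 at f = 1.

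| Profile day | Missed | AUC (f = 0.5 to 1.0) | CL/F (f = 0.5 to 1.0) |
|---|---|---|---|
| Monday | Sunday | −12% to −23% | +13% to +31% |
| Monday | Saturday | −4% to −9% | +5% to +10% |
| Monday | both | −16% to −32% | +19% to +48% |
| Thursday | both | −0.9% to −1.7% | +0.9% to +1.7% |
| Friday | both | −0.3% to −0.6% | +0.3% to +0.6% |

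The 24 h concentration (Cmin) after a Monday profile falls by 23% (Sunday), 9% (Saturday) or 32% (both).

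**Why f = 1 is a bound.** At f = 1 the model has one compartment. At steady state its highest possible Cmax is AUC × k/(1 − a) = 2287 × 0.0408/0.624 ≈ 149 ng/mL, about half the stated 296. Some of the AUC must lie outside a 17 h exponential. The stated figures do not fix f.

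**Scale.** The between-person CV of AUC is 685/2287 = 30%, so one missed Sunday dose moves AUC by 0.117/0.30 to 0.235/0.30, about 0.4 to 0.8 SD.

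**Half-life range (assumed 12 to 24 h).** A missed Sunday dose before a Monday profile costs 9% to 25% of AUC. Both doses missed before a Thursday profile cost at most 4.7%.

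**How many profiles.** If all 24 profiles were on Mondays and 5% of Sunday doses were missed (assumed), 24 × 0.05 = 1.2 profiles would be affected, and the chance of at least one is 1 − 0.95²⁴ = 71%. For 2% to 20%, the figures are 0.5 to 4.8 profiles and 38% to 99.5%.

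**Can the planned samples show it?** In a steady-state profile C0/C24 is 1. At 17 h it is (1 − 0.624)/(1 − 0.235) = 0.49 if Sunday was missed, and (1 − 0.235)/(1 − 0.088) = 0.84 if only Saturday was missed.

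**The case against.** The protocol contradicts nothing here. Day 28 is a target, and of the 11 days in the window, 8 (Wednesday to Saturday, twice) directly follow at least two observed weekday doses. Even at f = 1, both weekend doses missed would change CL/F by about 5% on a Wednesday. This stands: a reader might infer that the protocol fixes the profile on a Monday, and it does not.

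Weekend doses are not unchecked either. Pills are handed over at the preceding visit, same-day confirmation is requested, staff chase non-responders, and dates and times are confirmed again at the next meeting. This also stands, but every one of these checks rests on the participant's own report. Nor are weekends the only source of unobserved doses: sections 6.2 and 7.8 allow back-up and holiday self-dosing.

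A missed Sunday dose would probably show in the 0 h and 24 h samples, and an analysis plan that is not shown may say how to handle it. That limits the harm, so the absence of such a rule is not counted as a fault here. A Saturday-only miss would be harder to see. Detection afterwards would also cost the participant's only profile, whereas scheduling can prevent most of the problem.

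Finally, a strict rule with days 31 and 32 only could run out of eligible days before day 33. That is a fair warning about the form of the fix.

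**Conclusion.** This is a scheduling weakness of moderate size that is cheap to remove. At its target day the profile that yields the primary PK predictor follows the two least certain doses of the week, and nothing in sections 7.1, 7.7 or 8.7 directs it elsewhere.

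If a weekend dose is missed but reported as taken, a Monday profile overstates CL/F by about 13-31% (Sunday) or 19-48% (both), against a 30% between-person CV of AUC. A Thursday profile reduces the AUC loss from the same two misses to at most about 1.7% at 17 h.

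This rests on linear superposition, the stated half-life, the assumed range of f, and the Monday start applying in whichever period holds the 7 doses/week condition. A reader might infer that CL/F will be biased by 31% or 48%, or that the second primary objective fails. The documents support neither: those figures are upper bounds for single affected profiles, and no miss rate is given.

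**What to change.** In sections 7.1, 7.7 and 8.7, state that the PK profile should preferably start on a Thursday or Friday within the existing window. First choice is day 24 or 25 after the first dose, with day 31 or 32 as back-up, after at least three directly observed doses where feasible. Day 24 is 24 × 24/17 ≈ 34 half-lives after the first dose, so going early does not endanger steady state.

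If no such day is available, do the profile anyway. For every profile, record which preceding doses were observed and compare the 0 h and 24 h concentrations. Add a sensitivity analysis that leaves out profiles not at steady state, with the criterion set before results are seen.

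The cost is less freedom in booking the research unit; a Friday start also runs into Saturday. No dose, visit count or sample changes.

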## Drug-Administration Flowchart

| **Procedure** | **Weekly follow-up (6 wks)** | | | | | | |
| --- | --- | --- | --- | --- | --- | --- | --- |
|  | **M** | **T** | **W** | **Th** | **F** | **S** | **Su** |
| **DOT (7 doses/week)** | **X** | **X** | **X** | **X** | **X** |  |  |
| **Phone mDOT (7 doses/week)** |  |  |  |  |  | **X** | **X** |
| **DOT (4 doses/week)** | **X** | **X** |  | **X** | **X** |  |  |
| **DOT (2 doses/week)** |  | **X** | **X** |  |  |  |  |

## Screening

Enrollment criteria will be evaluated at a screening visit. Screening evaluations will be used to determine the eligibility of each candidate for study enrollment. Eligible participants will be enrolled within 45 days. If a participant fails to enroll within 45 days of the screening visit and wishes to participate in the study, s/he may repeat the screening visit procedures.

Potential study participants will be screened by a research clinician and counselor. Participants will be told the purpose of the study and the reasons they have been approached for participation. A clinician will explain study procedures, including potential risks with study participation, and answer the participant’s questions. When a subject agrees to participate, s/he will sign an English consent form. The informed consent process is designed to maximize understanding of potential risks. The participant will have an opportunity to ask questions during the informed consent process. Subjects will be provided a copy of the consent form and a copy of the UCSF Experimental Subjects’ Bill of Rights. Participants will be informed that they can decline to participate without any change in their relationship with UCSF or the San Francisco Department of Public Health. They will also be informed that they can quit the study at any time. To protect the autonomy of volunteers, participants will not be given any academic credit or advantage for participation.

After written informed consent is obtained, participants will receive a symptom- directed medical and physical exam, a rapid HIV test, and screening safety laboratory tests (CBC, electrolyte panel, serum creatinine, liver function tests, total serum lipase, phosphorus, hepatitis B surface antigen, hepatitis B core antibody, hepatitis B surface antibody, urinalysis, and urine pregnancy test for women). Individuals who have isolated hepatitis B core antibody positivity will also have Hepatitis B DNA testing. Laboratory tests that fall outside the eligibility range may be repeated once within the screening period based on clinician discretion. All potential participants will receive standardized pre- and post-test risk reduction counseling and HIV testing by an FDA-approved commercially available whole blood rapid HIV test. Reactive rapid HIV test results must be confirmed with both another FDA-approved EIA and Western blot (WB) or immunofluorescent assay (IFA). Subjects will be assessed for eligibility by the research clinician and PI according to the eligibility criteria listed in sections 5.3 and 5.4. To ensure adequate hair at each sampling, participants will be advised to leave at least 2 cm of hair growth when getting their hair cut during this study.

If the participant is unable to complete all the screening procedures in one visit, they may return for one or more visits to complete these procedures.

| **Screening visit (up to 45 days prior to Enrollment visit)** | |
| --- | --- |
| Component | Procedure/Analysis |
| Educational/  Administrative | - Review educational materials/study flipchart with participant - Obtain written informed consent for screening - Assign Screening ID - Collect demographic information - Collect locator information - Assess eligibility - Provide reimbursement for visit - Schedule screen 2 and/or enrollment visit |
| Clinical | - Collect medical history - Record list of concomitant medications - Perform symptom-directed physical exam - Provide counseling   - HIV pre- and post-test counseling |
| Urine | - Collect urine sample   - Qualitative hCG   - Dipstick UA (and full UA with microscopy if greater than trace protein, glucose, heme, or leukocytes) |
| Blood | - Collect blood samples   - Complete blood count   - Serum chemistries   - Liver function tests   - Total serum lipase   - Hepatitis B testing   - HIV-1 rapid test (confirmatory testing as needed) |

